## Abstract

Newly diagnosed breast cancer (BC) patients with clinical T1–T2 N0 disease undergo sentinel-lymph-node (SLN) biopsy, although most of them have a benign SLN. The pilot noninvasive lymph node staging (NILS) artificial neural network (ANN) model to predict nodal status was published in 2019, showing the potential to identify patients with a low risk of SLN metastasis. The aim of this study is to assess the performance measures of the model after a web-based implementation for the prediction of a healthy SLN in clinically N0 BC patients. This retrospective study was designed to validate the NILS prediction model for SLN status using preoperatively available clinicopathological and radiological data. The model results in an estimated probability of a healthy SLN for each study participant. Our primary endpoint is to report on the performance of the NILS prediction model to distinguish between healthy and metastatic SLNs (N0 vs. N+) and compare the observed and predicted event rates of benign SLNs. After validation, the prediction model may assist medical professionals and BC patients in shared decision making on omitting SLN biopsies in patients predicted to be node-negative by the NILS model. This study was prospectively registered in the ISRCTN registry (identification number: 14341750).

## 1. Introduction

Most breast cancer (BC) patients are diagnosed at an early stage of the disease, and surgery is the first treatment option for most patients [1]. As early BC is curable [2], the number of BC survivors is increasing, and both the short- and long-term sequelae of BC treatment are important. It is essential to carefully balance both the under- and overtreatment of BC. The benefits of a procedure must outweigh the harms, and we must strive for a high quality of life for BC patients during and after treatment. It is necessary to improve clinical algorithms to choose the most optimal treatment strategy while retaining a high level of safety for patients.

The number of nodal metastases is an important prognostic factor for survival in BC, as it is the most obvious distinction between node-positive and -negative BC [1]. Establishing the correct nodal status for BC patients affects decision making regarding the use of adjuvant chemotherapy and radiotherapy in early BC [3]. However, in the era of personalized treatment, the impact of prognostic information from axillary lymph node status on the medical decision-making process is less important than previously, and adjuvant treatment is increasingly tailored toward the biological and genetic features of BC [4].

Axillary ultrasound, the most used imaging modality for nodal assessment, is an unreliable staging modality for BC patients with a low nodal metastatic burden; its negative predictive value (60% to 90%) is not reassuring [5,6,7,8,9]. Different rates of sensitivity and specificity of axillary ultrasound are reported in the literature, ranging from 26% to 94% and from 53% to 98%, respectively [7,8,9,10,11]. Thus, for most BC patients presenting with a clinically and radiologically node-negative axilla at diagnosis, in the quest to reliably stage the axilla, the surgical sentinel-node procedure is routinely used for staging [12]. However, for BC patients aged >70 years with hormone-receptor-positive and human epidermal growth factor receptor 2 (HER2)-negative conditions, sentinel-lymph-node surgery is optional if the patient receives adjuvant endocrine therapy according to ASCO guidelines [12]. However, these guidelines are not implemented in Sweden, and the surgical management of the axilla is the same, independent of age at diagnosis and molecular subtype. In the majority (~80%) of early BC patients undergoing sentinel-node surgery, the procedure identifies only healthy lymph nodes with no metastatic tumor deposits [3,4]. For these patients, the invasive surgical procedure is diagnostic but not therapeutic.

Although there are many benefits of the minor surgical sentinel-node procedure compared to axillary dissection, sentinel-node surgery is associated with short- and long-term side effects. Most importantly, immediate postoperative swelling, paresthesia, arm lymphedema, and self-reported symptoms of arm swelling are documented complications of the sentinel-node procedure [13,14]. In addition, the procedure is time-consuming and requires financial healthcare resources.

We previously developed and published a decision-making tool, the noninvasive lymph node staging (NILS) prediction model, for the prediction of benign lymph nodes in primary BC [15]. The NILS prediction model, which is an artificial neural network (ANN) model, was developed using retrospectively collected variables (including patients, *n* = 800). The NILS prediction model includes ten top-ranked risk variables for nodal status (please refer to Section 2.1), including hormone receptor status but excluding molecular subtype. The aim of this study is to retrospectively validate the NILS prediction model in one temporal and one geographical cohort.

## 2. Materials and Methods

### 2.1. Study Design

This validation study of the NILS prediction model will be a multicenter, retrospective study based on prospectively collected clinicopathological variables included in patients’ medical charts, mammograms, and pathology reports. We plan to assess the external validity and model validity of the NILS prediction model for healthy lymph nodes and evaluate the discrimination and calibration of the NILS prediction model while following the TRIPOD statement [16]. A schematic schedule of enrollment, data collection, and monitoring is provided in Figure 1. This study aims to validate the NILS prediction model, a previously published ANN-based decision-making tool that is based on retrospectively collected data at Lund University Hospital, Sweden. In agreement with TRIPOD recommendations, the data in this validation study are derived from cohorts different in both time and study sites. Thus, patients who underwent surgery for primary BC in Malmö, Sweden, in 2020 (*n* = 400, a temporal validation cohort) and in Helsingborg, Sweden, between 2019 and 2020 (*n* = 200, a geographical external validation cohort) will be identified by a national registry of cancer diagnoses, treatments, and outcomes (INCA). The data retrieved from clinical files will include age at BC diagnosis, medical history of BC, ultrasound assessment of the axilla, and clinical status of the axilla. Tumor size and localization in the breast, including laterality, multifocality, and mode of tumor detection, will be obtained from imaging assessment reports (mammography, followed by ultrasound assessment in cases of an inconclusive mammographic report). In cases where multifocality is detected by either clinical examination or any imaging modality in this study, the tumor will be considered multifocal. Tumor biology data (estrogen receptor status, progesterone receptor status, HER2 status, molecular and histopathological subtype, vascular invasion, and proliferation index Ki-67) will be obtained using preoperative core needle biopsy. Number of metastatic axillary lymph nodes will be obtained from reports of surgical pathology specimens (sentinel-node surgery and axillary dissection).

The original NILS prediction model for nodal prediction includes ten top-ranked risk variables for nodal status (tumor size, vascular invasion, multifocality, estrogen receptor status, histological type, progesterone receptor status, mode of detection, age, tumor localization in the breast, and Ki-67 positivity) [15]. This validation study will validate the original model, including the aforementioned variables. In addition, important improvements from the early NILS prediction model are that we can validate the algorithm, include predictors that are only preoperatively available (i.e., data on biomarkers and histopathological subtypes from core-biopsy data rather than breast surgical specimens), and estimated tumor size by imaging rather than by histopathology in surgically removed tissue.

The decision-making calculator (the NILS prediction model) is derived from an ANN-based model for the prediction of benign lymph nodes at the time of diagnosis in primary BC. The ANN technique can decipher nonlinear and difficult-to-predict associations between risk variables and output. In addition, to handle missing values of important variables such as vascular invasion, an additional ANN model that can predict this value using other available variables was developed. A web-based implementation of the NILS protocol, the nodal status classifier, was developed and tested in a pilot cohort of newly diagnosed BC patients. This web interface is used in this study (Figure 2), providing an estimated probability of healthy lymph nodes for each study participant.

This study protocol was written according to SPIRIT guidelines [17].

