### 2.6. Power Calculation and Statistical Plan

We estimated that the sample size would be *n* = 300 study participants, and although each validation cohort will be assessed separately, the total number would be *n* = 600. Due to practical reasons (shortage of qualified research personnel at one of the study sites), we will include *n* = 400 from the temporal cohort and *n* = 200 from the geographical cohort. The area under the curve (AUC) for the original prediction model was 0.74 in a development cohort, where two-thirds of the patients were node-negative [15]. Assuming the same proportion of N0 and the same discrimination for future patients, the inclusion of 300 patients is sufficient to obtain 90% probability of reaching an AUC of at least 0.70 in this validation study. This calculation was based on the asymptotic normality of the AUC estimate and simulations that determined the relationship between the sample size and standard error of the AUC estimate. The performance of the ANN decision tool upon validation will be assessed in terms of discrimination (AUC) and calibration (comparison of the observed and predicted event rates of benign axillary nodal status, Hosmer–Lemeshow test). Separate analyses of patients undergoing breast-conserving surgery and mastectomy will be performed. No interim analyses will be performed. Patients will be screened for eligibility according to specified inclusion and exclusion criteria and subsequently included if all criteria are fulfilled. Study participants for whom mandatory variables for the NILS protocol are missing, i.e., variables that the ANN model cannot predict, will be excluded.

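### The sample-size statement carries over the development AUC of 0.74 unchanged although several inputs now have a different source, and the 0.04 margin leaves little room for any loss

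*Protocol article*

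**What the plan says.** Section 2.1 lists the ten predictors of the published network and states: "This validation study will validate the original model, including the aforementioned variables". The next sentence presents as improvements that biomarkers and histological subtype come from core biopsy instead of the surgical specimen, and that the study uses "estimated tumor size by imaging rather than by histopathology in surgically removed tissue". The same section takes vascular invasion in this study from core biopsy and describes an additional network "to handle missing values of important variables such as vascular invasion", which works from the other variables. The only item it lists from the surgical pathology reports is the number of metastatic axillary nodes.

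Section 2.6 bases the sample size on the AUC that "for the original prediction model was 0.74 in a development cohort", "where two-thirds of the patients were node-negative". The premise is stated openly: "Assuming the same proportion of N0 and the same discrimination for future patients". The conclusion is that "the inclusion of 300 patients is sufficient to obtain 90% probability of reaching an AUC of at least 0.70 in this validation study". The planned cohorts are 400 (temporal) and 200 (geographical), each assessed separately.

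**The concern.** The 0.74 belongs to the model as developed. By the article's own account, several inputs to the tool under validation are now measured differently, and one predictor may be filled in from the others. A value predicted from the other available variables adds little or no independent information on nodal status. It is therefore reasonable to ask whether the same discrimination can be expected, and Section 2.6 makes no allowance for the change.

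Two things are at stake. First, the 90% depends on an AUC only 0.04 above the target, so a small loss would matter. Second, the label affects what the result may be said to show. A good AUC would support the web tool with preoperative inputs. A lower AUC could reflect the inputs, the period or the hospital, because all of these change together and the article describes no same-patient comparison.

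**Working it through.** **Inputs.** True AUC 0.74, two-thirds node-negative, target 0.70 and n = 300, all from Section 2.6. Cohorts of 400 and 200, from Sections 2.1 and 2.6. The article gives no AUC with preoperative inputs, so values from 0.70 to 0.73 are assumptions. The two-thirds share is held fixed, so that only the AUC varies.

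**Formula.** Section 2.6 names its method: "asymptotic normality of the AUC estimate and simulations that determined the relationship between the sample size and standard error". In the same spirit, P(estimate ≥ 0.70) = Φ((A − 0.70)/SE), with the Hanley–McNeil standard error

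SE² = [A(1 − A) + (n₁ − 1)(Q₁ − A²) + (n₀ − 1)(Q₂ − A²)]/(n₀n₁), where Q₁ = A/(2 − A), Q₂ = 2A²/(1 + A), n₀ is the number node-negative and n₁ the number node-positive.

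**Step 1: the plan's own figure.** For A = 0.74, n₀ = 200 and n₁ = 100:
- Q₁ = 0.5873, Q₂ = 0.6294, A² = 0.5476.
- SE² = (0.1924 + 99 × 0.0397 + 199 × 0.0818)/20,000 = 0.00102, so SE = 0.0319.
- P = Φ(0.04/0.0319) = Φ(1.25) = 89.5%.

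Exchanging the two groups in the formula gives SE = 0.0285 and 92.0%. A binormal simulation with 20,000 replicates gives SE = 0.0299 and 90.8%. The stated 90% is reproduced. The margin of 0.04 is 0.04/0.0319 ≈ 1.3 standard errors.

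**Step 2: other true AUCs.** For A = 0.72 and n = 300: SE² = (0.2016 + 99 × 0.0441 + 199 × 0.0844)/20,000 = 0.00107, SE = 0.0327, P = Φ(0.02/0.0327) = Φ(0.61) = 73%. The rest follow in the same way (267/133 patients at n = 400, 133/67 at n = 200):

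| True AUC (0.70–0.73 assumed) | n = 300 (stated basis) | n = 400 (temporal) | n = 200 (geographical) |
|---|---|---|---|
| 0.74 | 90% | 93% | 85% |
| 0.73 | 82% | 86% | 78% |
| 0.72 | 73% | 76% | 69% |
| 0.71 | 62% | 64% | 60% |
| 0.70 | 50% | 50% | 50% |

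The choice of standard error matters little. With the simulated 0.0299 (obtained at 0.74), a true AUC of 0.72 at n = 300 gives Φ(0.02/0.0299) = Φ(0.67) = 75%. The shortfall at n = 200 with AUC 0.74 comes from the uneven split of the cohorts and has nothing to do with the inputs.

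**Step 3: numbers needed for 90%.** By the same formula: 314 patients at 0.74, 572 at 0.73 and 1,313 at 0.72. A larger cohort is not a practical answer to a loss of 0.02.

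**Step 4: illustration of a loss.** Assume a binormal score to which the new inputs add independent error, giving reliability r. The AUC becomes Φ(√r × Φ⁻¹(0.74)). For r = 0.9 this is 0.729 (82% at n = 300). For r = 0.8 it is 0.718 (70%). The values of r are assumptions; nothing in the article estimates them.

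**The case against.** The change of inputs is disclosed and sensible. The abstract gives the aim as performance after web implementation with preoperatively available data, and Section 2.1 says the web interface is used. The phrase about the original model can be read as meaning the ten-variable model, with the next sentence explaining how its inputs are obtained. Section 2.6 labels its premise as an assumption, and any sample-size statement weakens when the assumed effect is lowered. No test or decision rule hangs on 0.70; the AUC will be estimated and reported in any case. Most of this stands. It reduces the point to one of labelling and of showing how sensitive the probability is.

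Three stronger readings are tempting, and the article does not support them:
- *That both of the first-listed predictors, size and vascular invasion, changed source.* Section 2.1 states the change for size, biomarkers and histological subtype. It gives core biopsy as the source of vascular invasion in this study but does not say where it came from in development. A change there is an inference. How often the second network is needed is not stated either.
- *That 0.74 is shown to be too high.* Different inputs, a predicted predictor and a development-cohort estimate all point downward, but that is a judgement on direction. The article mentions a pilot test of the web tool and gives no results from it.
- *That an unexplained drop would undermine the study.* Specimen inputs are not available when the decision on sentinel-node biopsy is made. A valid primary result does not require input error to be separated from failure to transport.

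A full protocol exists and is not public, so further specimen data may be collected without being listed here.

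**Conclusion.** The point holds as a matter of labelling and sensitivity. Section 2.1 names the original model as the object of validation while changing the source of at least three kinds of input, and Section 2.6 transfers the development AUC without allowance for that. The 90% is correct for 300 patients under its premise, but 300 is the size of neither cohort. For the cohorts that will be analysed, the premise itself gives 93% and 85%. An assumed loss of 0.01 gives 86% and 78%, and a loss of 0.02 gives 76% and 69%. These figures rest on a two-thirds node-negative share and the Hanley–McNeil approximation. The size of any actual loss cannot be known from the article, and the text does not say whether the network was refitted or kept frozen for the preoperative inputs. The validity of the primary analysis is not in question.

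**What to change.** (a) In Sections 2.1 and 2.6, name the validated object as the web tool with preoperative inputs and say whether the network is the published one, frozen. Replace the single 90% by the probability of reaching 0.70 at n = 400 and n = 200 for true AUCs from 0.70 to 0.74. This costs a few lines of text.

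(b) As a secondary analysis, record specimen tumour size, and specimen vascular invasion and biomarkers where reported, from the surgical pathology reports already opened for nodal counts. Run the same model on these inputs in the same patients and give the paired AUC difference with its confidence interval (DeLong). Present it as descriptive. A difference of 0.02 is smaller than the standard error of a single AUC at 0.74 in either cohort (0.0277 at n = 400, 0.0391 at n = 200). Pairing will narrow this, by an amount that depends on a correlation not yet known, but the estimate will still be imprecise.

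(c) Report the AUC separately for patients with observed and with network-predicted vascular invasion, also as descriptive. This needs only a flag in the dataset.

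The cost is some added data entry and one further model run. Section 3.2 shows that data entry has already begun, so (b) means going back to completed records, and Section 2.6 reports a shortage of research staff at one site. If that is too much, (a) and (c) can be done alone. The primary analysis stays as planned.

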### 2.2. Definition of pN0

In this study, pN0 is defined as sampled axillary lymph nodes with no invasive cell clusters of >0.2 mm at the largest diameter (presence of isolated tumor cells, i.e., tumor cell clusters that are ≤0.2 mm at the largest diameter, are considered pN0). 

### 2.3. Ethical Approval

All procedures performed in studies involving human participants were in accordance with the ethical standards of either the institutional or national research committee and with the 1964 Declaration of Helsinki and its later amendments or comparable ethical standards. This study was approved by the Regional Ethics Committee in Lund, Sweden (committee reference number: 2021-00174).

Patients received information about the study through advertisements in the local press, and the patients were allowed to opt out. The ethical committee waived the requirement for informed consent and consent for publication. Upon receiving treatment for BC at the hospitals, the patients provided their consent to register in INCA. The local department for personal data admission at the hospital (KVB Samråd, Region Skåne, Sweden) granted the researchers access, with digital logging, to patients’ digital medical charts. Access to the web calculator is protected by usernames and passwords, which provides permission to authorized users only (physicians, research nurses, and research administrators) from the principal investigator.

### 2.4. Study Population

Each included patient underwent standard diagnostic work-up for the clinical treatment of BC, including a clinical examination, mammogram, ultrasound, and preoperative core biopsy of their tumor. At the time of surgery, the patients underwent standard procedures according to the decision made at the multidisciplinary conference, and surgical specimens comprising the resected breast tumor and axillary lymph nodes were pathologically examined. No extra diagnostic or interventional procedures were performed within this validation study of a retrospective cohort. No results will be reported to the treating physician or study participants.

### 2.5. Participating Centers

Data are retrieved from two independent centers in southern Sweden: Malmö, a university hospital, and Helsingborg, a regional hospital. There were 0.75 million and 0.3 million people in the catchment areas of the breast surgical clinics of Malmö and Helsingborg, respectively.

### 2.6. Power Calculation and Statistical Plan

We estimated that the sample size would be *n* = 300 study participants, and although each validation cohort will be assessed separately, the total number would be *n* = 600. Due to practical reasons (shortage of qualified research personnel at one of the study sites), we will include *n* = 400 from the temporal cohort and *n* = 200 from the geographical cohort. The area under the curve (AUC) for the original prediction model was 0.74 in a development cohort, where two-thirds of the patients were node-negative [15]. Assuming the same proportion of N0 and the same discrimination for future patients, the inclusion of 300 patients is sufficient to obtain 90% probability of reaching an AUC of at least 0.70 in this validation study. This calculation was based on the asymptotic normality of the AUC estimate and simulations that determined the relationship between the sample size and standard error of the AUC estimate. The performance of the ANN decision tool upon validation will be assessed in terms of discrimination (AUC) and calibration (comparison of the observed and predicted event rates of benign axillary nodal status, Hosmer–Lemeshow test). Separate analyses of patients undergoing breast-conserving surgery and mastectomy will be performed. No interim analyses will be performed. Patients will be screened for eligibility according to specified inclusion and exclusion criteria and subsequently included if all criteria are fulfilled. Study participants for whom mandatory variables for the NILS protocol are missing, i.e., variables that the ANN model cannot predict, will be excluded.

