### 3.1. Significance

Internationally, there are numerous artificial intelligence projects involving the noninvasive identification of N0 BC. The NILS protocol uses easily accessible clinicopathological variables, including mammography data, and, in contrast to many other algorithms, does not require medical imaging data for machine learning analysis. We present a robust validation study of the NILS prediction model based on two external cohorts. If the accuracy and discrimination reach a satisfactory level, our prediction tool (the NILS protocol) can be implemented and would assist medical professionals and BC patients in shared decision making on omitting sentinel-node biopsy in patients predicted to be node-negative. In the future, the use of the NILS protocol may save healthcare resources and reduce both costs and unbeneficial side effects. In addition, the NILS prediction model and our presented validation study may prompt future studies of nodal metastases of malignancies in other organs; thus, it may have implications beyond BC. 

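### The 90% probability of an AUC of at least 0.70 belongs to one cohort of 300; with separate cohorts of 400 and 200 it is about 93–95% and 85–87%, and about 78–83% for both

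*Protocol article*

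**What the plan says.** All the design figures are in Section 2.6 of the protocol article. The AUC "for the original prediction model was 0.74 in a development cohort", "where two-thirds of the patients were node-negative". "Assuming the same proportion of N0 and the same discrimination for future patients", the section concludes that "the inclusion of 300 patients is sufficient to obtain 90% probability of reaching an AUC of at least 0.70 in this validation study". The stated method is a normal approximation to the AUC estimate, with its standard error found by simulation.

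The 300 is a per-cohort size: "although each validation cohort will be assessed separately, the total number would be" 600. The same section then departs from equal sizes because one site is short of research staff, and sets 400 for the temporal and 200 for the geographical cohort. No probability is given for either of these sizes.

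The Introduction gives the purpose in terms of both cohorts: "The aim of this study is to retrospectively validate the NILS prediction model in one temporal and one geographical cohort".

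**The concern.** The sentence attaches the 90% to the study as a whole, but the calculation behind it is for one sample of 300. The study consists of two separate assessments, and neither has that size. The temporal cohort is larger than planned and so does better than 90%. The geographical cohort is one-third smaller than planned and so does worse. It is also the cohort that the article calls the geographical external validation. If the aim is read as validation in both cohorts, the relevant probability is the joint one, which is lower than either cohort's own figure.

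A reader who takes the 90% at face value will overestimate how likely the geographical cohort is to reach 0.70, and will overestimate further how likely both cohorts are to do so. That matters when a geographical AUC somewhat below 0.70 has to be interpreted: even if the model performs exactly as assumed, this would happen in about 13–15% of such studies (100% minus 85–87%), not 10%.

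**Working it through.** **Inputs**, all from Section 2.6: true AUC 0.74; two-thirds N0; target 0.70 for the point estimate; 90% at n = 300; actual sizes 400 and 200.

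**Formula.** With a normal approximation, P(estimated AUC ≥ 0.70) = Φ((0.74 − 0.70)/SE) = Φ(0.04/SE).

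**Step 1: reproduce the 90% at n = 300 (200 N0, 100 N+).** The simulated standard error is not reported, so four routes were used.

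- *Back-solved:* 90% requires 0.04/SE = 1.2816, so SE = 0.04/1.2816 = 0.0312.
- *Hanley–McNeil:* SE² = [A(1−A) + (n₁−1)(Q₁−A²) + (n₂−1)(Q₂−A²)]/(n₁n₂), with Q₁ = A/(2−A) = 0.5873, Q₂ = 2A²/(1+A) = 0.6294 and A² = 0.5476. With N0 as the positive class, SE = 0.0285 and the probability is 92.0%. With N+ as the positive class, SE = 0.0319 and the probability is 89.5%.
- *Equal-variance binormal simulation, 20,000 replicates:* SE = 0.0299, probability 90.8%.

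The 90% is therefore sound as a figure for one cohort of 300 (89.5–92.0%).

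**Step 2: use the actual sizes.** The back-solved SE scales with 1/√n: 0.0312 × √(300/400) = 0.0270; 0.0312 × √(300/200) = 0.0382; 0.0312 × √(300/600) = 0.0221. The other routes were recomputed at each size.

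| | Back-solved | Hanley–McNeil, N0 positive | Hanley–McNeil, N+ positive | Simulation |
|---|---|---|---|---|
| n = 300 (plan) | 90.0% | 92.0% | 89.5% | 90.8% |
| n = 400, temporal | 93.1% | 94.8% | 92.6% | 93.8% |
| n = 200, geographical | 85.2% | 87.4% | 84.7% | 86.3% |
| n = 600, one sample | 96.5% | 97.7% | 96.2% | 96.6% |

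**Step 3: joint probability.** The cohorts contain different patients, so for a given true AUC the probabilities multiply. Back-solved: 0.931 × 0.852 = 0.793. Over the other routes: 0.926 × 0.847 = 0.784 up to 0.948 × 0.874 = 0.829. At the intended 300 + 300 the back-solved figure would have been 0.90 × 0.90 = 0.81. Most of the gap between 90% and the joint figure thus comes from having two cohorts; the unequal split takes about 2 points more.

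**Sensitivity.** The Introduction puts the share of early breast cancer patients with only healthy sentinel nodes at about 80%. If that share applied here in place of two-thirds, Hanley–McNeil gives 88.1–92.7% at n = 400 and 79.8–84.8% at n = 200. Jointly this is 0.881 × 0.798 = 0.70 to 0.927 × 0.848 = 0.79. This is a departure from the plan's assumption, shown only for direction.

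**The case against.** The strongest reply is that the 90% carries its own denominator. The sentence names 300 patients, the preceding text makes clear that this is per cohort, and the figure reproduces. On this view only the closing words about the study are loose. The reply is right about the arithmetic at 300. It does not rescue the statement, because the same section has already replaced 300 with 400 and 200 and gives no figure for either.

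A second reply is that this is an estimation study. The value 0.70 appears only in the sample-size reasoning; the assessment sentence in Section 2.6 and the primary endpoint in Section 2.9.1 set no threshold, and the abstract speaks of reporting performance. This stands, and it limits the point. A reader might infer that each cohort is to pass or fail at 0.70, and that with no rule for combining them the same data could be called a success or a failure. The documents do not support that reading. The sentence "If the accuracy and discrimination reach a satisfactory level, our prediction tool (the NILS protocol) can be implemented" is discussion prose that names neither a number nor a cohort. A rule for combining the cohorts, if one is needed, may be in the full protocol or analysis plan, which is not shown. Reporting the two cohorts separately is a legitimate design, and a difference between them would be informative about transportability.

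It also follows that the joint probability is the study's chance of success only if validation in both cohorts is what the study sets out to show. The Introduction's aim suggests this but does not make it a criterion.

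**Conclusion.** The point holds as a misattributed figure. The 90% is correct for one cohort of 300 and for nothing that the study will actually analyse. At the planned sizes the probability of an estimated AUC of at least 0.70 is about 93–95% (temporal), about 85–87% (geographical), about 78–83% (both) and about 96–98% (all 600 as one sample). The statement is thus somewhat cautious for the temporal cohort, about 3 to 5 points too high for the geographical cohort, and about 7 to 12 points too high for the two jointly.

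These figures rest on a true AUC of 0.74 in both cohorts, two-thirds N0, a normal approximation for the estimate and independent cohorts; the ranges reflect the choice of standard error. It does not follow that the plan allows contradictory conclusions or contains a faulty pass/fail rule, since no such rule is stated. Nor does the finding put the planned analyses themselves in question.

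**What to change.** In Section 2.6, replace the single 90% with the probability for each cohort at its actual size, recomputed with the sponsor's own simulated standard errors: about 93–95% at n = 400 and about 85–87% at n = 200. If the study aims to show validation in both cohorts, add the joint probability, about 79% when back-solved from the plan's 90% (range 78–83%). State in the same place whether 0.70 is a success criterion or only a planning target and, if it is a criterion, which cohort result or results decide.

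This takes a few sentences and a rerun of an existing calculation, with no further patients or data. The downside is that the stated probability becomes less favourable for the geographical cohort and for the joint result.
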